### Sample size

Depression has an estimated annual prevalence of 8.3 % in adolescents [12], and between 8 % and 20 % of young people in community samples develop depression over an 18-month period [51–53]. On the basis of the age of the current sample, together with the timing of the intervention (before a major, universal stressor), we expect that onset rates will be high (up to 15 %). Calculations of required sample size for the primary outcome measure were based on detecting a post-intervention effect size of 0.20 in combined analyses of data collected from 2015 and planned 2016 cohorts. This estimate is based on previous depression prevention research using an online intervention [54]. Although the expected effect is small, it reflects the universal nature of this intervention. Power was set at 0.80, α = 0.05 (two-tailed) and a correlation of 0.5 assumed between baseline and endpoint scores. To allow for possible clustering effects (i.e., participants from the same school having characteristics and outcomes more alike than between schools), a design effect [55] was calculated assuming an intraclass correlation coefficient (ICC) of 0.02 and an average class size of 25. The estimate of the ICC was derived from a previous Australian school-based study that found a non-significant ICC of 0.02 [54]. The estimated sample size was 1166. The target size sample size was set at 1600, or 800 students per condition, to accommodate an attrition rate of approximately 20 % (see [56]). This translates to approximately 50 students (or 2 classes) per school in 30 schools. An interim analysis of students in the 2015 cohort will involve approximately 300 students per arm. Under the assumptions outlined above, there will be 80 % power to detect an effect size of 0.40 standard deviations between groups.

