### Analysis

Primary analyses will be undertaken on an intention to treat basis, including all participants as randomised, regardless of treatment actually received. Effectiveness of SPARX-R will be established using a planned contrast of change from pre-test to the post-intervention in the active compared with placebo condition on the MDI within a mixed-effects model repeated-measures analysis [104]. School will be included in analyses as a random effect to evaluate and accommodate clustering effects. Variables used in determining allocation balance will be evaluated and retained in analyses where they are significant or quasi-significant. An unconstrained variance–covariance matrix will model within-individual dependencies. Transformation of scores, including categorisation, may be undertaken to meet distributional assumptions and accommodate outliers. Contrasts comparing change on the MDI from pre-test to other occasions of measurement will be undertaken as secondary analyses.

Models for binary outcomes analogous to the primary analysis approach will be used to compare the prevalence rates (MDD status) and other dichotomous outcomes between the two treatment arms at the endpoint and other occasions of measurement. Relative and absolute risk reduction, NNT (see [105]) and other relevant indices will be calculated for these outcomes and undertaken separately for participants who did not meet criteria for caseness at pre-test to assess the effect of the intervention on incidence. In analyses of scaled secondary variables, we will use methods comparable to those of the primary analysis. Subsidiary complier and related analyses will estimate the efficacy of SPARX-R in participants who completed modules from the SPARX-R program to produce a clinical impact (estimated to be four or more modules) [36]. In exploratory analyses, we will examine the effects of moderators and mediators of treatment (see [106]).

Interim analysis of outcomes of the 2015 cohort will be undertaken following the methods described above. Although the sample available will be of limited size, the outcome of this analysis will be used to guide the second stage of the trial, planned for 2016. Should there be clear evidence of lack of effect, based point estimates of effectiveness and associated confidence intervals, consideration may be given to abandoning second-stage recruitment or seeking possible modifications of the intervention.

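### Read literally, the single school random effect cancels from the pre-to-post change contrast, so the primary test does not carry school-level clustering of change

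*Protocol article*

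**What the plan says.** The Analysis section of the protocol article fixes three parts of the primary model:

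- The test: "Effectiveness of SPARX-R will be established using a planned contrast of change from pre-test to the post-intervention", comparing the arms on the MDI in a repeated-measures mixed model.
- The school term: "School will be included in analyses as a random effect to evaluate and accommodate clustering effects".
- The covariance over time: "An unconstrained variance–covariance matrix will model within-individual dependencies".

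It names no school-by-occasion effect, cluster-robust variance or school-based degrees of freedom. Change from pre-test to the other occasions is tested as a secondary analysis, scaled secondary outcomes use comparable methods, and the 2015 interim analysis follows the same methods. Confidence intervals from that interim may inform whether second-stage recruitment goes ahead.

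The Sample size section targets "detecting a post-intervention effect size of 0.20 in combined analyses of data collected from 2015 and planned 2016 cohorts" and applies a design effect "assuming an intraclass correlation coefficient (ICC) of 0.02 and an average class size of 25". The Randomisation section makes the school the unit of allocation.

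**The concern.** In a school-randomised trial, the variance of the treatment contrast must include whatever students in the same school share on the quantity being tested. Here that quantity is change. A school effect that is the same at every occasion describes schools that are persistently higher or lower. It says nothing about schools whose students improve or worsen together. The flexible covariance, which could describe this, is placed only within the individual.

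There is reason to expect some shared change: the sessions run in class, and each school timetables them to suit itself (Procedures section). If shared change exists and the model omits it, the primary confidence interval is too narrow and false positives are too frequent. The other MDI change contrasts, the scaled secondary outcomes analysed as change, and the interim intervals inherit the fault.

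**Working it through.** **Inputs from the Sample size section.** "Power was set at 0.80, α = 0.05 (two-tailed) and a correlation of 0.5 assumed between baseline and endpoint scores"; effect 0.20 SD; ICC 0.02; cluster size 25; target 1600 in 30 schools, set "to accommodate an attrition rate of approximately" 20%. Analysed: 1600 × 0.8 = 1280, or 1280/30 = 42.7 per school. **Assumed, because not given:** the correlation ρ between a school's effects at pre and post, and that the ICC of 0.02 applies to each occasion.

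**1. The plan's own figure.** With r = 0.5, the variance of change is 2(1 − 0.5) = 1 SD². A t-based calculation for 0.20 SD gives 394 per arm, 788 in total. The design effect is 1 + 24 × 0.02 = 1.48, and 788 × 1.48 = 1166. This agrees with "The estimated sample size was 1166". The ANCOVA variance, 1 − r², gives 873 and does not. An unadjusted post-score variance is also 1, so 1166 cannot tell the two apart.

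**2. The cancellation.** Under a school intercept with variance τ² and student covariance Σ, the covariance of a school's (pre, post) means is Σ/m + τ²J, where J is the 2 × 2 matrix of ones. For change, c = (−1, 1) and c′Jc = 1 − 2 + 1 = 0. The model variance is c′Σc/m, with τ² absent.

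**3. What is left out.** If school effects correlate ρ over time, the between-school variance of change is 2 × 0.02 × (1 − ρ). Divided by the total variance of 1, this is the ICC of change. The true variance exceeds the model's by about DE = 1 + 41.7 × ICC of change, and type I error = 2[1 − Φ(1.96/√DE)].

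| ρ | ICC of change | DE | Type I error, formula | Simulated (two runs) |
|---|---|---|---|---|
| 1.0 | 0 | 1.00 | 5.0% | 5.1% (one run) |
| 0.9 | 0.004 | 1.17 | 7.0% | not run |
| 0.8 | 0.008 | 1.33 | 9.0% | 7.9%, 8.8% |
| 0.5 | 0.020 | 1.83 | 14.8% | 15.7%, 15.3% |
| 0 | 0.040 | 2.67 | 23.0% | 23.1%, 22.4% |

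The simulations fitted the literal model by REML (1500 and 1000 trials per setting). At ρ = 0.5 the mean model standard error was 0.056 against an empirical SD of 0.076. With 53 per school and 20% of post scores missing, the error was 15.6%, so incomplete data do not rescue the model. Using t with 28 df while keeping the model still gave 13.7%. A t-test on school-mean change gave 4.7% to 5.8% across the settings of the larger run.

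**4. Interim.** About 300 per arm in the 10 schools of the Trial status section is 60 per school. At an ICC of change of 0.02, DE = 1 + 59 × 0.02 = 2.18 and type I error is 18.4% (simulated 18.2%).

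**5. Power once clustering of change is carried.** At an ICC of change of 0.02 and 1280 analysed, SE = √(4 × 1.833/1280) = 0.0757 and 0.20/0.0757 = 2.64. Power is 75% by the normal approximation and 72% with t on 28 df. At an ICC of change of 0.008, SE = √(4 × 1.333/1280) = 0.0645, 0.20/0.0645 = 3.10, and power is about 87% by the normal approximation. The model without the term would suggest 95% in both cases.

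**The case against.** The strongest reply is that the article never says the school effect is an intercept only. It says the term is there to evaluate and accommodate clustering, a school-by-occasion effect would do that, and a full analysis plan that is not shown may specify one. This stands in part: the conclusion is conditional on the literal reading. But the article does set out the covariance structure, and it puts the part that is free over time at student level. A statistician following that text would fit a model that does not do what the text says the school term is for.

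Three stronger readings are tempting, and the document supports none of them.

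- A reader might infer that the trial's type I error is 15%. That needs ρ = 0.5, which is nowhere stated. The same students are measured before and after a programme of about 5 to 7 weeks, and school traits such as selective status persist, which points towards higher ρ and a smaller error. School-specific delivery points the other way. Neither settles the value.
- A reader might infer that the Sample size section contradicts the Analysis section by inflating this same contrast for clustering. It does not say whether the ICC of 0.02 refers to levels or to change, and at r = 0.5 the figure of 1166 fits both.
- A reader might extend the fault to every outcome. The cancellation concerns change contrasts. It does not show a fault in the comparisons of prevalence at an occasion, or in academic rank, which is obtained once.

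**Conclusion.** The point holds in conditional form. As written, the primary model has no term for school-level clustering of change, so its standard error is right only if school effects are perfectly stable from pre to post. Under an ICC of 0.02 per occasion, r = 0.5, 30 equal schools and about 43 analysed per school, type I error runs from 5% to 23% over ρ from 1 to 0. At ρ = 0.5 the standard error is too small by a factor of √1.83 = 1.35. This is a fault in the stated model rather than a missing detail, but its actual size cannot be fixed from the document.

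**What to change.** State in the Analysis section that the model includes a school-by-occasion random effect, with school effects free to differ and to correlate across occasions, and that the contrast is tested with degrees of freedom based on the number of schools. Alternatively, analyse school-mean change. Changing the degrees of freedom alone is not enough. Use the same structure for the other MDI change contrasts, for scaled secondary outcomes analysed as change, and for the 2015 interim intervals.

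The text change is small, but it has a statistical cost. Intervals widen by an amount that depends on ρ, and little is lost if school effects prove stable. If the ICC of change is 0.02, power for 0.20 SD with 30 schools and 1280 analysed is about 72%, partly because a randomised school contributes about 43 students, not the 25 used in the design effect. The Sample size section should say whether its ICC refers to levels or to change, and restate the 80% under that assumption.

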## Methods/Design

### Trial design

This study is a cluster randomised controlled superiority trial with two parallel arms, consisting of an experimental condition and an attention-matched control condition. We will employ an adaptive design, such that accumulating data will be used to decide if or how to modify the study as it continues. To facilitate this design and to stagger recruitment, the trial will take place in two stages across consecutive years, with each stage beginning at the start of the academic calendar (February 2015 and February 2016). The intervention phase will last 5 weeks with a follow-up period of 18 months. Results from the 2015 cohort will be subject to an interim analysis to determine preliminary effects and determine whether any modifications are required in the conduct of the trial in 2016. Feasibility of continuation will also be assessed at this stage in terms of student and teacher acceptability of the intervention and any implementation issues that may arise during the first year of the trial.

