### Randomisation

Each participating school (cluster) will be randomised to complete the SPARX-R or lifeSTYLE program. School-level randomisation will be used to avoid contamination between conditions, for the ecological validity of providing the intervention at the cluster level and for practical convenience. A statistician not involved in the implementation of the trial will randomly allocate schools using the allocation sequence outlined below. The identity of schools will be concealed from the statistician during this process.

Randomisation in cluster randomised trials is problematic because the number of clusters involved is usually relatively small. In large, individually randomised trials, balance in the makeup of each arm is achieved as a function of the numbers involved. Balance between arms can be achieved by stratification or minimisation [57]. Stratification can accommodate only a limited number of balancing variables, and minimisation is based on incremental assignment of participants to groups. In TriPoD, the number of potentially relevant variables to be balanced between arms is quite large (e.g., sex, number of enrolled students, Index of Community Socio-Educational Advantage school index, language background other than English), and all available sites will be enumerated before commencement of the trial. Achieving approximately equal numbers of participants in each arm is also an aim of the allocation design, as this will determine the study’s power in the absence of substantial clustering effects. Accordingly, this attribute of each school will be used not to estimate the degree of balance, but rather to screen potential grouping after balanced combinations have been selected.

We will use the method developed and implemented by Carter and Hood [58] to ensure balance between intervention arms. This enumerates all possible divisions of the available schools into two groups and calculates a balance index [59] for each of these groupings. The 10 most balanced groupings will be retained after excluding any grouping resulting in a deviation of more than 10 % in predicted individual participant sample size between inventions. The allocation schedule will be selected at random from the groupings retained.

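### The primary model keeps the variables that restricted the randomisation only if they prove significant or quasi-significant, so it is not fixed in advance; the effect falls mainly on the 10-school interim analysis

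*Protocol article*

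**What the plan says.** **Allocation.** The Randomisation section of the protocol article describes a tightly restricted draw of schools: "This enumerates all possible divisions of the available schools into two groups and calculates a balance index [59] for each of these groupings". It continues: "The 10 most balanced groupings will be retained after excluding any grouping resulting in a deviation of more than 10" per cent in predicted sample size between arms. Finally: "The allocation schedule will be selected at random from the groupings retained". The balancing variables are given by example: "sex, number of enrolled students, Index of Community Socio-Educational Advantage school index, language background other than English".

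**Primary test.** The Analysis section defines it as a "planned contrast of change from pre-test to the post-intervention in the active compared with placebo condition on the MDI", in a mixed model for repeated measures with school as a random effect.

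**Covariates.** The rule in the same section is: "Variables used in determining allocation balance will be evaluated and retained in analyses where they are significant or quasi-significant". No threshold is given for quasi-significant. Nor is it said whether a main effect or an interaction with occasion is evaluated.

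**Stages.** Under Trial design, "the trial will take place in two stages across consecutive years". The Analysis section applies the same methods to the interim analysis of the 2015 cohort, which Trial status puts at 10 schools.

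**The concern.** Drawing the allocation from the best-balanced groupings removes most of the between-arm variation due to the balancing variables. A model that contains them credits this to the standard error. A model that omits them leaves their variation in the error term, so its standard error is too large whenever they are prognostic.

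The stated rule commits to neither model. It looks at the outcome data and keeps whichever variables pass an unstated cut-off. With few schools, the variables that pass are partly those that happen to fit. The residual variance is then too small, and the degrees of freedom are counted as if the retained set had been chosen beforehand.

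At stake are the validity of the primary standard error and a primary model that two analysts could specify differently after seeing the same data. This matters most in the 2015 cohort. Its point estimates and confidence intervals may lead to abandoning stage-two recruitment or to changing the intervention, and intervals that are too narrow let a lack of effect look clearer than it is.

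**Working it through.** **1. The plan's own sample size.** Sample size section: effect 0.20, power 0.80, two-sided α 0.05, baseline-endpoint correlation 0.5, ICC 0.02, class size 25.
- SD of change = √(2(1−0.5)) = 1.
- n per arm = 2(1.960+0.842)²/0.20² = 392.4, so 393. The t-based solution is 393.4, so 394.
- Design effect = 1+(25−1)×0.02 = 1.48.
- Total = 2×394×1.48 = 1166.2, the stated 1166.

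The stated size thus corresponds to a change score without covariates. It does not depend on the retention rule.

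**2. How tight the restriction is.** Ten schools divide equally in C(10,5)/2 = 126 ways, so 10 retained groupings are 7.9% of them. Twenty schools divide in 92,378 ways, so 10 are about 0.01%.

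**3. Hand check of omitting the variables.** Assume 50 students per school and half of the school variance explained.
- Variance of a school mean: 0.02+0.98/50 = 0.0396.
- With the explained part removed: 0.01+0.98/50 = 0.0296.
- Ratio of standard errors: √(0.0396/0.0296) = 1.157.

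Under near-perfect balance, the unadjusted test rejects only beyond 1.157 times the usual critical value:
- 10 schools, 8 df: 2.306×1.157 = 2.67, giving type I error 0.028 (simulated 0.029).
- 30 schools, 28 df: 2.048×1.157 = 2.37, giving 0.025 (simulated 0.021).

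**4. Simulated type I error at nominal 0.05.** School means were generated with four independent normal school variables and total ICC 0.02. Each stage drew one grouping from the 10 best balanced, and the test used residual df. The 10-school stage enumerated every split; the 20-school stage used 20,000 sampled splits. Monte Carlo SE is about 0.002 (10 schools) and 0.0035 (30 schools).

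| Schools | School variance explained | None kept | All kept | Keep p<0.05 | Keep p<0.10 | Keep p<0.20 |
|---|---|---|---|---|---|---|
| 10 | 0% | 0.053 | 0.051 | 0.071 | 0.081 | 0.093 |
| 10 | 50% | 0.029 | 0.053 | 0.057 | 0.072 | 0.087 |
| 10 | 80% | 0.019 | 0.049 | 0.052 | 0.067 | 0.080 |
| 30 | 0% | 0.051 | 0.051 | 0.055 | 0.057 | 0.062 |
| 30 | 50% | 0.021 | 0.050 | 0.048 | 0.051 | 0.053 |
| 30 | 80% | 0.014 | 0.055 | 0.052 | 0.055 | 0.057 |

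A further run of the rule with 30 schools ranged from 4.6 to 6.7%.

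**5. Interval coverage at the interim.** Covariates were selected in a model that contains the treatment term, so the selection does not depend on the true effect, and coverage is one minus type I error. For 10 schools that is 1−0.093 = 90.7% to 1−0.052 = 94.8%.

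**6. Power at d = 0.20, 30 schools, 50% explained.** None kept 0.77; rule 0.84 to 0.86 across the three cut-offs; all kept 0.86. With 43 per school:

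| School variance explained | None kept | Rule | All kept |
|---|---|---|---|
| 25% | 0.72 | 0.76–0.78 | 0.76 |
| 50% | 0.76 | 0.82–0.84 | 0.83 |
| 90% | 0.79 | 0.91–0.92 | 0.92 |

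**The case against.** Several stronger readings are tempting, and the documents do not support them.

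- **That the rule costs the trial power.** A reader might set the none-kept column against the all-kept column. The plan does not prescribe dropping everything. It drops only variables that fail the cut-off, and under that rule power matches full adjustment.
- **That the final p-value is badly inflated.** With 30 schools it is not.
- **That analysts may choose among all covariate sets.** Taking the smallest treatment p-value over the 16 subsets of four variables gave 10.5% in a 10-school simulation. The plan selects covariates on their own significance, so that figure does not describe it. Sixteen is not fixed either. The list is only by example, and the Randomisation section suggests that participant numbers screen groupings rather than enter the balance index.
- **That 9% is the error rate of the interim decision.** The interim has no stated p<0.05 success rule. It looks for clear lack of effect from estimates and intervals, so the consequence is interval width.
- **That stage is ignored.** The Setting section says school type will be accounted for. That sentence concerns partially selective schools, but school type largely tracks stage. Stage itself is not named, and no text calls it an allocation block. Separate allocation is inferred from the two start years.

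Two technical objections stand as limits. A stable school effect largely cancels in change, so a balancing variable matters only through its interaction with occasion, and the documents give no variance share for that. The main simulation also left out the 10% size screen. In a 10-school run with an assumed spread of school sizes, adding it moved the unadjusted type I error from 2.8% to 3.5% and did not reduce the inflation from selection.

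**Conclusion.** The point holds in a limited form. The Analysis section states a data-driven rule with an undefined cut-off for the variables that restricted the randomisation, so the primary MDI model is neither fixed in advance nor tied to the design. This is a stated rule, not detail left to an analysis plan.

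- **10-school interim:** type I error about 5 to 9%, rising as the cut-off loosens, against about 5% with fixed adjustment. Nominal 95% intervals cover about 91 to 95%.
- **30-school analysis:** about 5 to 6.5%, with essentially no power lost against full adjustment.
- **Prognostic variables left out altogether:** conservative, 1.4 to 2.1% with 30 schools when they explain 50 to 80% of school variance, and about 9 points of power lost at 50% (0.77 against 0.86).

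The number of variables, their variance share and the cut-offs are assumptions, because the documents give none of them. The school-level ICC of 0.02 is the protocol's, applied here to change. The inflation at 10 schools appears at every variance share tried, though at p<0.05 it is slight once the variables explain half or more. The conservatism of omission needs prognostic variables.

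**What to change.** Replace the retention sentence with a fixed rule. The variables that enter the balance index, listed by name, plus stage or school type, go into the primary model as fixed covariates whatever their significance. Because the contrast is on change, their interactions with occasion must be included. State whether enrolment belongs to the index or serves only as the size screen.

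For the 10-school interim, name a short list in advance, at most two variables. Four would cut the school-level df from 8 to 4 and raise the critical value from 2.31 to 2.78; two leave 6 df (2.45). Report the model without these covariates as a sensitivity analysis, noting that it is conservative if they are prognostic.

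A permutation test over the retained groupings would match the design but cannot stand alone in the 2015 cohort. With 10 groupings its smallest two-sided p-value is 0.10, or 0.20 if mirror images count separately.

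**Cost.** Wording only: no new data, and 1166 is unchanged. At 30 schools, four variables and stage take the school-level df from 28 to 23 (critical value 2.05 to 2.07). Power falls slightly if the variables turn out not to be prognostic.

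### Balance covariates are kept or dropped on their outcome p-values with no stated cut-off, so the data choose the model; at the 10-school interim this can make confidence intervals too narrow

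*Protocol article*

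**What the plan says.** The Randomisation section allocates schools by a highly constrained method. It says that "the number of potentially relevant variables to be balanced between arms is quite large" and gives examples ("e.g., sex, number of enrolled students, Index of Community Socio-Educational Advantage school index, language background other than English"). A balance index is computed for every possible split of the schools. "The 10 most balanced groupings will be retained after excluding any grouping" that is too unequal in predicted participant numbers, and one of the ten is drawn at random. Every site is listed before the trial starts, so the balance variables are known before any outcome exists.

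The Analysis section bases effectiveness on a "planned contrast of change from pre-test to the post-intervention" in the MDI, from a mixed model for repeated measures. On clustering it says: "School will be included in analyses as a random effect to evaluate and accommodate clustering effects". On covariates it says: "Variables used in determining allocation balance will be evaluated and retained in analyses where they are significant or quasi-significant". It gives no threshold for *quasi-significant*. Scaled secondary outcomes use comparable methods, and the interim uses the same ones: "Interim analysis of outcomes of the 2015 cohort will be undertaken following the methods described above". The interim's point estimates and confidence intervals may lead the investigators to consider dropping the second stage or changing the intervention. Trial status gives 2 + 8 = 10 schools for that cohort.

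By contrast, the Setting section promises to account for school type with no condition about significance.

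**The concern.** Screening covariates on their p-values in the outcome data means that the model is not fixed before the result is seen, and an elastic threshold leaves room for choice. Two errors can follow, in opposite directions.

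- **Too narrow.** With few schools, a variable that passes the screen has often done so because it happens to absorb school-to-school variation. The residual school variance is then understated, and so is the standard error.
- **Too wide.** Constrained allocation has already removed a balance variable's contribution from the true error of the arm contrast. If a prognostic balance variable is then screened out, the model's standard error still carries that contribution.

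At stake are the prespecification of the primary model and the trustworthiness of the interim intervals that inform whether stage two goes ahead.

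**Working it through.** **1. The plan's own figure.** The covariate rule has no number attached, so the sample size serves to check the scale. With "detecting a post-intervention effect size of 0.20", 80% power, two-sided 5% and r = 0.5, the change-score variance is 2(1 − 0.5) = 1. The t-test then needs 394 per arm. The design effect is 1 + 24 × 0.02 = 1.48, and 2 × 394 × 1.48 = 1166.2. The stated 1166 is reproduced.

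**2. Inputs.**
- From the protocol: ICC 0.02; 30 schools of about 50; at the interim 10 schools and about 300 per arm, so 600 / 10 = 60 per school; allocation drawn from the best-balanced splits.
- Assumed: four school-level candidates; *quasi-significant* taken as p ≤ 0.10 with backward elimination; candidates explaining a share R² of 0, 0.5 or 0.9 of between-school variance; equal school sizes; the 30 schools allocated in one step.

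**3. Expected standard error without covariates.** The variance of a school mean is 0.02 + 0.98/m.
- 10 schools of 60: √[(1/5 + 1/5)(0.02 + 0.0163)] = 0.121.
- 30 schools of 50: √[(1/15 + 1/15)(0.02 + 0.0196)] = 0.073.

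The simulation returns both values.

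**4. Coverage of nominal 95% intervals** (school means, school-level t, no treatment effect, 4000 replicates, Monte Carlo SE about 0.0035):

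| Schools | R² | Screened | All four kept | None kept |
|---|---|---|---|---|
| 10 | 0 | 0.906 | 0.946 | 0.949 |
| 10 | 0.5 | 0.905 | 0.949 | 0.970 |
| 10 | 0.9 | 0.913 | 0.950 | 0.984 |
| 30 | 0 | 0.945 | 0.951 | 0.950 |
| 30 | 0.5 | 0.950 | 0.949 | 0.977 |
| 30 | 0.9 | 0.955 | 0.954 | 0.992 |

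With 10 schools and R² = 0, the screened model's average SE is 0.108 against a true SD of 0.124. Since 0.108 / 0.124 = 0.87, it is about 13% too small. The last column is the limit in which every balance variable is dropped. It shows the direction of the second error, not the size it has under the plan's rule.

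**5. Other screens at 10 schools.** A 0.20 cut-off gives 0.893–0.907 (R² 0 and 0.5). A one-shot screen at 0.10 gives 0.925–0.931.

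**6. Inference method at 10 schools** (p ≤ 0.10, backward):

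| Interval | Screened | All four kept |
|---|---|---|
| School-level t, variance free | 0.905–0.913 | 0.946–0.950 |
| School-level t, school variance ≥ 0 | 0.940–0.979 | 0.976–0.994 |
| Normal, school variance ≥ 0 | 0.889–0.940 | 0.911–0.959 |

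The bound matters because the SE cannot then fall below √(0.4 × 0.0163) = 0.081. With the 0.20 cut-off, the bound and school-level t, the screen covers 0.929–0.959.

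**7. Repeat run** (four candidates, p ≤ 0.10). At 10 schools the false-positive rate is 9–10% under the screen against about 5% with all four kept when the variance is free, and 4.4–5.6% under the screen when it is bounded. At 30 schools it is 4.7–6.6% against 4.5–5.7%. With eight candidates, a number the protocol does not give, a further simulation at 30 schools put it at 5.8–7.2%.

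**8. How the covariates enter.** A school-level variable entered only as a main effect adds the same amount before and after the intervention, so it cancels from the change. In one simulated complete data set the arm-by-time estimate was −0.10412 with and without main effects (SE 0.0799 and 0.0798). It moved to −0.138 only when by-occasion terms were added. Some of these fits gave convergence warnings, so they serve as illustration only.

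**The case against.** The strongest reply is that little harm reaches the planned analysis. A reader might infer from the screening rule that intervals are too narrow throughout the trial. The figures do not support that: at 30 schools with four candidates, coverage is close to nominal.

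A reader might also take a 9–10% interim error rate as a property of the plan. It is not. It needs an unbounded school-level residual variance, whereas the plan uses a mixed model with school as a random effect. With a non-negative school variance and school-level degrees of freedom, coverage is near nominal. With normal-based intervals the shortfall returns, but the fixed model falls short too. The article does not state the degrees-of-freedom method, and may properly leave it to the SAP. If covariates enter only as main effects, the screen barely touches the change contrast at all. The candidate set may also be smaller than four, because the Randomisation section uses participant numbers to screen groupings rather than to score balance.

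Two further inferences fail. One calculation gives 73–76% power without the prognostic variables against 77–86% with them. It drops those variables altogether, which is not the plan's rule, so no power loss from the rule itself is shown. Nor do the interim intervals decide continuation mechanically: the text asks for clear signs of no effect and then only allows abandonment or modification to be considered. No probability of wrongly stopping has been computed.

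These replies limit the size of the problem. They do not defend the rule. Choosing covariates on outcome p-values is something that the article states, not a detail left out of it. An SAP that supplied a cut-off would still let the outcome choose the model.

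**Conclusion.** The point holds in a limited form, and the sentence should be changed. The outcome data, through a screen with no stated threshold, choose the model for the primary contrast, the scaled secondary outcomes and the interim, although the variables could be fixed before allocation.

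- **Interim, 10 schools:** coverage can fall to about 90–91% under school-level t intervals, four candidates and p ≤ 0.10. It is near nominal with a bounded school variance and school-level degrees of freedom.
- **Full trial, 30 schools, four candidates:** coverage is about 94.5–95.5%. The fault there is a model driven by the outcome, not a demonstrated coverage failure.
- **Either stage:** screening out a prognostic balance variable after constrained allocation makes the interval too wide.

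The number of candidates, the cut-off, the form of the screen and the R² values are assumptions. The covariates are also assumed to act on change, that is, to enter by occasion.

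**What to change.** Replace the sentence with:

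> A short list of the school-level variables used in the balance index (two to four, named before any comparison of arms) is included, with its by-occasion terms, in every primary and secondary model whatever its p-value; no variable is added or removed on significance.

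At the interim use one or two of these, also fixed in advance. Report any model selected on p-values only as a sensitivity analysis.

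No new data are needed. The cost is a few school-level degrees of freedom. If the variables prove irrelevant, power at 30 schools fell from 72.9% to 71.6% in simulation (30 schools with 43 completers each), a loss of 1.3 points. Interim intervals will be somewhat conservative where the school variance is bounded at zero: with all four variables kept they covered 0.976–0.994. The version with one or two variables was not simulated.
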